### Study population

The study setting includes 21 municipalities in Denmark, all of which are situated in the North Denmark Region (*n* = 6) or Region of Southern Denmark (*n* = 15) (see Fig. 1). Denmark consists of a total of five regions. The two selected regions have some of the highest proportions of mothers who are of young age and/or have a low educational attainment. Each of the 21 participating municipalities constitutes a cluster in the trial.

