##### Intensified intervention

In the intervention arm, families in which the mothers are younger than 25 years when they give birth (young age) and/or have primary school or vocational training as their highest educational attainment (low education) are offered an intensified intervention following the same breastfeeding principles, but they will receive a higher dose of the intervention. The aim is for health visitors to be proactive in delivering support and preventing breastfeeding cessation in this group, which carries an increased risk of early cessation. The intensified intervention is delivered within the first five months through additional follow-up phone calls (*n* = 7) and a single extra visit, all of which are scheduled to occur in-between the home visits (see details in Additional File 1). If a mother receiving follow-up by telephone ceases breastfeeding, she will no longer receive the telephone follow-up. Families accepting the intensified intervention are free to decline further extra telephone calls and/or visits.

The intervention is expected to reach > 6,000 families in the trial period, of whom 30–40% are expected to be in the target group for the intensified intervention. After the trial period, health visitors in the control clusters will receive the training and supportive materials developed during the intervention.

Figure 2 presents the programme theory in a logic model structure. The programme theory guides evaluation by outlining our hypothesis as to which mechanisms drive intended changes in outputs and outcomes to be measured, e.g., the hypothesis that the breastfeeding support programme will promote frequent breastfeeding, which will increase the likelihood of establishing effective breastfeeding, among others because milk production is stimulated causing sufficient milk to reach the infant, which, in turn, is hypothesised to lower the risk of readmissions.

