### Multidisciplinary evaluation data

#### Difference-in-Difference design using register data

In the National Child Health Register, municipalities have been required to report data on exclusive breastfeeding since 2011. Difference-in-difference analyses will be applied to estimate the difference in change in proportions breastfeeding at four months, and in average number of weeks of breastfeeding from before (≤ 2021) to after (≥ 2022) the intervention period comparing the intervention and control arm. The advantage of this approach is that it will provide an estimate of the effect if treatment is upscaled to the entire country. The effect of the intensified intervention in the difference-in-difference analyses will be examined by including an interaction term like in the survey analyses. Data from national Danish registers will be retrieved on all mother–child dyads in the included 21 municipalities from 2015 to 2025. This part of the evaluation awaits data availability in the registries which is expected in early 2025 at the earliest. Table 3 provides information on the registers used.

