A trial is only as good as methods and design applied. Therefore, we have carefully considered our choices and based them on current knowledge and MRC recommendations [32]. To achieve as high as possible a response rate in the survey conducted among parents, questionnaire items have been carefully chosen based on the proposed mechanisms of change displayed in the programme theory (Fig. 2) and we made sure to minimise the length of the questionnaire. To reduce the risk of selection bias, only few exclusion criteria were applied; i.e., we applied only those criteria that contributed to elucidate differences in the likelihood of succeeding with breastfeeding or that were a safety hazard to the infant. In this way, we may have strengthened the generalisability of the findings. Moreover, the contents of the support might vary according to context, be it organizational or personal, e.g., the skills of the individual health visitors.

One strength of this study is that data will be collected in two regions of Denmark that have some of the lowest breastfeeding rates and in 21 different municipalities. This will reduce the risk of recruitment bias and allow comparisons by context of outcomes and processes, thereby extending generalisability to other settings. Another strength is that data on individuals lost to follow-up will be retrieved from registers, providing the opportunity to analyse important differences between individuals retained in the study and those who dropped out. Linkage to register data will provide further possibility to assess recruitment bias as we will identify all women assessed versus those not assessed for eligibility [51, 59].

A potential confounder of the results is that health visitors may shift employment between municipalities in the two trial arms and that mothers in the intervention clusters might have relations with mothers in control clusters, all of which may potentially cause some contamination by relaying breastfeeding-related information from the intervention group to mothers in the control group. Furthermore, the website used constitutes a specific risk as it is password protected by a generic, easily shared code only. The role of these potential risks of bias will be assessed. Furthermore, the design of the study does not allow for concealment of allocation group.

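### The difference-in-difference estimate is described as the effect of national upscaling, but it applies to all births in the 21 trial municipalities, whose mix of mothers differs from the country's

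*Protocol article*

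**What the plan says.** The section on the difference-in-difference design names one advantage of the approach: "it will provide an estimate of the effect if treatment is upscaled to the entire country". The same section says the register data will cover "all mother–child dyads in the included 21 municipalities from 2015 to 2025", and that the contrast is the change from before (2021 or earlier) to "after (≥ 2022) the intervention period comparing the intervention and control arm". It also plans an interaction term for the intensified intervention, as in the survey analyses.

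On who lives in those municipalities, the Study population section places 6 of them in one region and 15 in another, and notes that "Denmark consists of a total of five regions". It adds: "The two selected regions have some of the highest proportions of mothers who are of young age and/or have a low educational attainment". The Discussion describes the setting as "two regions of Denmark that have some of the lowest breastfeeding rates". The sample size section gives the 2016 four-month figures as 49% in the project regions and 56% nationally.

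On effect size by group, the Objectives state the expectation that a higher dose will produce a stronger effect in mothers who are young or have low educational attainment. The Intensified intervention section says that, of the families the intervention should reach, "30–40% are expected to be in the target group for the intensified intervention".

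**The concern.** An average effect over a population depends on who is in it. The protocol says that its regions contain an unusually large share of one group of mothers. It also says that it expects the intervention to work better in that group. Taken together, these statements mean that the average over the 21 municipalities is not, in general, the average for Denmark. No reweighting of the difference-in-difference estimate to the national population is described. The inverse probability weighting in the Statistical methods section concerns missing survey outcomes and selection into the survey, which is a different problem.

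What is at stake is interpretation. A national decision maker would look for an upscaling estimate, and the article promises one without qualification. If the protocol's own hypothesis is right, the figure reported under that label would tend to be too favourable for the country.

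**Working it through.** **Inputs from the protocol article**
- Target-group share where the intervention is delivered, s_reg: 30–40% (Intensified intervention). It is stated for families reached by the intervention. I use it for the 21 municipalities as a whole.
- Effect in the target group, E_high: 45% to 55%, so 10 points (Sample size and power calculations). This is a power scenario, not a prediction.
- Overall ambition: 49% to 56%, so 7 points, stated as an odds ratio of 1.32 (same section).

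**Inputs not in the documents (assumed)**
- National target-group share, s_nat: 20–30%.
- Effect in other mothers, E_low: either 4 points, or the value that makes the regional average 7 points.

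**The plan's own figure.** (0.56/0.44) / (0.49/0.51) = 1.2727 / 0.9608 = 1.325. This agrees with the stated 1.32, so there is no numerical error in the plan on this point.

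**Formula.** Average effect = s × E_high + (1 − s) × E_low. The gap between the regional and national averages is therefore

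(s_reg − s_nat) × (E_high − E_low).

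It is zero if the shares match or if the two effects are equal. It is positive when the regional share is larger and the effect is stronger in the target group, and its sign would reverse if the effect were weaker there. The formula takes effects within each group to be the same in all regions.

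**Scenario A: E_low assumed to be 4 points**
- Regional, s_reg = 30%: 0.30 × 10 + 0.70 × 4 = 5.8 points.
- Regional, s_reg = 40%: 0.40 × 10 + 0.60 × 4 = 6.4 points.
- National, s_nat = 20%: 0.20 × 10 + 0.80 × 4 = 5.2 points.
- National, s_nat = 30%: 5.8 points.
- Overstatement: from 5.8 − 5.8 = 0 to 6.4 − 5.2 = 1.2 points.

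**Scenario B: regional average held at 7 points**
- E_low = (7 − 10 × s_reg) / (1 − s_reg). At 30% this is 4/0.70 = 5.7 points; at 40% it is 3/0.60 = 5.0 points.
- s_reg = 40%, s_nat = 20%: national average 0.20 × 10 + 0.80 × 5.0 = 6.0, an overstatement of 1.0 point.
- s_reg = 30%, s_nat = 30%: national average 7.0, an overstatement of 0.

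**Does the lower starting rate matter by itself?** Apply the same odds ratio at the national rate: odds 0.56/0.44 × 1.325 = 1.686, which is a proportion of 62.8%, or +6.8 points. At 49% the gain is +7.0 points. The difference of about 0.2 points is small, so the point rests on the mix of mothers and not on the baseline.

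**The case against.** The strongest defence is that the sentence contrasts register data with survey data. The survey depends on eligible, consenting mothers, with 80% expected participation and 30% attrition by four months, whereas the register analysis takes every mother–child dyad. Read this way, upscaling means delivery to everyone rather than to survey responders, and that advantage is real. It stands, but only within the 21 municipalities. The sentence names the entire country, and the Discussion makes only the weaker claim of extending generalisability to other settings.

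A second defence is that the planned interaction already yields group-specific effects. That is true and makes the remedy cheap, but no step applies national shares to those effects, and the promise of a national estimate carries no condition.

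A reader might infer several stronger points that the documents do not support:
- **That the regions were picked because of low breastfeeding rates or high risk.** The article calls the regions selected and describes their mix of mothers, but gives no reason for the choice. It reports the low rates as a feature and a strength of the setting. The argument needs only the mix, not the motive.
- **That the lower baseline is a second material source of bias.** On the protocol's own odds ratio it adds almost nothing.
- **That a national cost-effectiveness figure will be inflated.** The Health economic assessment section plans no national figure and does not say that its ratios use this estimate.
- **That a bias of a particular size has been shown.** The size rests on assumed inputs, and the range includes zero.

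**Conclusion.** The stated property is not one that the described analysis has. The analysis estimates the effect among all births in the 21 municipalities. To read it as the national effect requires either equal effects in the two groups of mothers, which the protocol hypothesises against, or matching group shares, which its description of the regions makes unlikely. Under the protocol's hypothesis the error would tend towards overstatement.

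The size cannot be fixed from the documents. The 0 to 1.2 and 0 to 1.0 point ranges are illustrations that depend on the assumed national share, on treating 10 points as the target-group effect, and on the assumed effect in other mothers.

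This is a minor point about the interpretation of a supplementary analysis. The randomised arm comparison, the validity of the difference-in-difference contrast within the 21 municipalities and the primary survey analysis are untouched.

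**What to change.** Restate the estimate as the effect among all births in the 21 participating municipalities, and keep the legitimate advantage that it does not depend on survey participation.

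If a national figure is wanted, take the two group-specific estimates from the planned interaction (young and/or low-educated mothers, and all others) and combine them using the national shares of those groups. Report the result as a standardised estimate, and state that it assumes equal effects within each group across regions.

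The cost is one revised sentence and, for the national figure, two national shares and a weighted combination of estimates already planned. No new trial data are needed. The downside is a possibly smaller and more qualified headline figure.

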#### Process evaluation

The implementation of the intervention will be analysed by process evaluation. The analysis will focus on barriers to and facilitators of the intervention, and on the dose, delivery and fidelity of the delivered intervention. Data utilised for this purpose will be quantitative and qualitative. Quantitative data will include survey data from health visitors, the health visitor records and a survey of organisational structures; and qualitative data will include interviews with families (*n* = 10), online focus group discussions with health visitors (*n* = 3), observations of breastfeeding support in the intervention clusters (*n* = 2–3), and dialogue meetings held with health visitor representatives from intervention clusters (*n* = 8).

Data from health visitors’ survey and the organisational survey will help us gain insight into any potential contamination between trial arms carried by health visitors changing employment from intervention clusters to control clusters.

#### Realist evaluation

A realist evaluation will be conducted to explore how the intervention works. Thorough analysis of the mechanisms that the intervention activates to produce the desired outcomes in the families of the intervention group will be conducted. The evaluation will highlight what works for whom under which circumstances. Qualitative data produced in individual interviews with parents (*n* = 25), observations of breastfeeding support (*n* = 30), focus group discussions with health visitors (*n* = 6) and field notes from dialogue meetings with health visitors (*n* = 10 +) will be analysed to identify the relationship between context, mechanisms and outcomes (so-called CMO configurations) [54]. We will conduct realist interviews to examine our programme theory and the causal assumptions on which it is rooted.

#### Health economic assessment

The health economic evaluation will shed light on the total health economic consequences of the intervention, including the intensified intervention. The health economic evaluation will be conducted as a cost-effectiveness analysis measuring health benefits as changes in the proportion of women breastfeeding at four and/or six months postpartum; and as a cost-utility analysis measuring the mothers’ gained quality-adjusted life years (QALYs). We measure QALYs using the widely used EQ-5D survey. QALYs include considerations related to both physical and mental well-being [55].

In both analyses, we assess two types of costs. First, direct costs related to the intervention will be assessed. Here, we distinguish between costs associated with the adaptation of the intervention and costs associated with its operation. Adaptation costs are fixed costs that are unlikely to be incurred by potential future adopters, whereas operating costs are repeated which is why separate reporting of cost types is relevant. Second, we will estimate the indirect costs (or savings) of the intervention. Like for indirect costs, we estimate the impact of the intervention on subjects’ healthcare usage in the primary and secondary healthcare sector. Such usage includes GP services and hospital admissions for both mother and child. We will consider the longest possible follow-up period. Both when considering breastfeeding and QALYs, we report the incremental effectiveness ratio (ICER). The ICER will establish the cost required to increase the share of breastfeeding mothers by a specific percentage and the cost accrued per gained QALY. Summarizing the cost-effectiveness of the intervention using ICERs allows for comparison with other healthcare interventions. Additionally, we will conduct a series of subgroup analyses to evaluate if the cost-effectiveness of the intervention depends on family characteristics.

### Patient and public involvement

The intervention was developed based on a previous successful study [27] and on a needs assessment [30] in a co-creation design with one to two health visitor representatives from each of the intervention clusters. The development was conducted in an iterative manner where health visitors tested aspects of the intervention in their real-world setting after having attended each meeting. The intervention was developed within a two-step approach: first, the contents and major outlines of the intervention were developed (January 2021 – April 2021). Next, co-creation with health visitor representatives from the intervention clusters was conducted following the described iterations (April 2021 – December 2021).

To be able to reduce social inequality in breastfeeding, it is important to investigate how the Breastfeeding Trial works in families who carry a high risk of early breastfeeding cessation, i.e., conceptualised in this study as families in which the mother is young or has a low educational attainment. These characteristics are in many ways stigmatised in high-income settings like Denmark [56, 57]. Therefore, it is essential that the intervention supports relationship built on trust and provides a sense of security between the health visitor and the family. In an effort to avoid this stigma, recruitment videos developed and employed as part of the intensified intervention were tested among mothers in the target group and revised according to their feedback. Additionally, parents in the risk group participated during the questionnaire development phase with testing of questionnaires, which generated valuable input for the process.

A reference group of parent organisations, practitioners and decision makers will be established in order to contribute knowledge and experience, qualifying the project and in the long term facilitating and ensuring the dissemination of the project and ensuring that the knowledge produced will be targeted the audience including relevant decision makers.

During monthly dialogue meetings, health visitors will have the opportunity to disclose information about any harms or adverse effects. As the intervention aims to strengthen existing standard care, it is not expected to induce harm to the study population, and no data monitoring committee has been established.

### Dissemination

The findings from the study will be reported in international peer-reviewed scientific journals and at national and international conferences. Moreover, participating municipalities, funding bodies, state and local governments and other stakeholders will be invited to participate in a national conference where the study findings will be presented. The Vancouver authorship guidelines will be adhered to and the appropriate CONSORT reporting guideline will be used when reporting the study findings.

ClinicalTrials.gov registration: NCT05311631.

## Discussion

This article outlines a cluster-randomised trial designed to increase breastfeeding duration and reduce social inequality in breastfeeding among Danish women – a population with a high uptake and long duration of breastfeeding compared with high-income countries around the world [4]. Results from Cochrane reviews have shown that healthcare services’ supportive practices may increase the duration of exclusive breastfeeding [2] which may be even further prolonged by heightening the frequency of the support offered to families in the early postpartum period [23] when cessation rates peak [58]. Occasionally, providing equal opportunities for all will not render equal outcomes. Therefore, the present trial adopts an equity approach in which those with higher risks are offered a higher dose of the intervention.

The MRC framework for complex intervention recommends that researchers go beyond investigating whether an intervention works by asking broader research questions identifying other impacts it might have, how the intervention works taking into account the context, and also considering how emerging evidence may be used to support decision making [32]. As such, the evaluation of a large intervention like the present study may benefit from taking a multiple methods stance. Besides applying an effectiveness approach, a realist evaluation will provide knowledge about how the intervention works, for whom it works and under what circumstances [36]. Furthermore, a health economic analysis will provide knowledge about whether the intervention is cost effective compared to other breastfeeding promotion interventions as well as other early-life intervention and other health interventions in general.

A trial is only as good as methods and design applied. Therefore, we have carefully considered our choices and based them on current knowledge and MRC recommendations [32]. To achieve as high as possible a response rate in the survey conducted among parents, questionnaire items have been carefully chosen based on the proposed mechanisms of change displayed in the programme theory (Fig. 2) and we made sure to minimise the length of the questionnaire. To reduce the risk of selection bias, only few exclusion criteria were applied; i.e., we applied only those criteria that contributed to elucidate differences in the likelihood of succeeding with breastfeeding or that were a safety hazard to the infant. In this way, we may have strengthened the generalisability of the findings. Moreover, the contents of the support might vary according to context, be it organizational or personal, e.g., the skills of the individual health visitors.

One strength of this study is that data will be collected in two regions of Denmark that have some of the lowest breastfeeding rates and in 21 different municipalities. This will reduce the risk of recruitment bias and allow comparisons by context of outcomes and processes, thereby extending generalisability to other settings. Another strength is that data on individuals lost to follow-up will be retrieved from registers, providing the opportunity to analyse important differences between individuals retained in the study and those who dropped out. Linkage to register data will provide further possibility to assess recruitment bias as we will identify all women assessed versus those not assessed for eligibility [51, 59].

A potential confounder of the results is that health visitors may shift employment between municipalities in the two trial arms and that mothers in the intervention clusters might have relations with mothers in control clusters, all of which may potentially cause some contamination by relaying breastfeeding-related information from the intervention group to mothers in the control group. Furthermore, the website used constitutes a specific risk as it is password protected by a generic, easily shared code only. The role of these potential risks of bias will be assessed. Furthermore, the design of the study does not allow for concealment of allocation group.

